## Abstract

**Background:**

Diabetes mellitus is an increasingly prevalent metabolic disorder that is associated with substantial disease burden. Australia has an opportunity to improve ways of caring for the growing number of people with diabetes, but this may require changes to the way care is funded, organised and delivered. To inform how best to care for people with diabetes, and to identify the extent of change that is required to achieve this, the Diabetes Care Project (DCP) will evaluate the impact of two different, evidence-based models of care (compared to usual care) on clinical quality, patient and provider experience, and cost.

**Methods/Design:**

The DCP uses a pragmatic, cluster randomised controlled trial design. Accredited general practices that are situated within any of the seven Australian Medicare Locals/Divisions of General Practice that have agreed to take part in the study were invited to participate. Consenting practices will be randomly assigned to one of three treatment groups for approximately 18 to 22 months: (a) control group (usual care); (b) Intervention 1 (which tests improvements that could be made within the current funding model, facilitated through the use of an online chronic disease management network); or (c) Intervention 2 (which includes the same components as Intervention 1, as well as altered funding to support voluntary patient registration with their practice, incentive payments and a care facilitator). Adult patients who attend the enrolled practices and have established (≥12 month’s duration) type 1 diabetes mellitus or newly diagnosed or established type 2 diabetes mellitus are invited to participate. Multiple outcomes will be studied, including changes in glycosylated haemoglobin (primary outcome), changes in other biochemical and clinical metrics, incidence of diabetes-related complications, quality of life, clinical depression, success of tailored care, patient and practitioner satisfaction, and budget sustainability.

**Discussion:**

This project responds to a need for robust evidence of the clinical and economic effectiveness of coordinated care for the management of diabetes in the Australian primary care setting. The outcomes of the study will have implications not only for diabetes management, but also for the management of other chronic diseases, both in Australia and overseas.

**Trial registration:**

Australian New Zealand Clinical Trials Registry (ACTRN12612000363886); World Health Organisation (U1111-1128-0481).

## Background

Diabetes mellitus is a chronic metabolic disorder that poses a significant health care problem in both developed and developing countries around the world, including Australia. An estimated 366 million people are affected by diabetes worldwide, and the incidence and prevalence of diabetes continues to rise, with more than 552 million people expected to be affected by the disorder by 2030—an increase of 51 percent [1]. People with diabetes are at risk of developing a range of complications, including chronic renal disease, diabetic eye disease and cardiovascular disease [2]. The impact of diabetes on the health system is considerable (in terms of both financial and human resources), with four percent of hospitalisations, 3.7 percent of general practitioner visits and 7.2 million prescriptions in Australia in 2009–10 attributed to the condition [3]. Direct and indirect health care costs related to the management of diabetes in Australia were estimated at AU$3.1 billion (excluding Commonwealth benefits) for type 2 diabetes (in 2001–02) [4], and at least $430 million for type 1 diabetes (in 2004–05) [5]. The chronicity and prevalence of diabetes, and the complications associated with the disorder, mean that diabetes will become an increasingly large burden on the health system, and on society, if new and more effective ways to manage it are not identified.

Australia has a unique opportunity to find better ways of caring for people with diabetes. Despite clear clinical objectives, fewer than fifty percent of people diagnosed with diabetes achieve the recommended targets for glycosylated haemoglobin, blood pressure and blood lipids [6-11]. Although care planning has been shown to result in substantial improvements in clinical and process outcomes for people with diabetes [12], almost eighty percent of GPs believe that the current care planning system involves too much red tape [13]. As a result, only eighteen percent of people with diabetes complete the recommended annual cycle of care [14], and approximately seventy percent do not have a multidisciplinary care plan at all [15].

To inform how best to care for people with diabetes, and to identify the extent of change that is required to achieve this, the Australian Government established the Diabetes Care Project (DCP)—a three-year, cluster randomised controlled trial that will test the impact of two different models of care (in comparison with usual care) on clinical quality and patient and provider experience. These models of care are designed to evaluate a number of evidence-based changes that the National Health and Hospital Reform Commission (NHHRC) [16] and the National Diabetes Advisory Group have identified as having the potential to improve the way care is organised and delivered. These changes include: (1) the introduction of new funding models, such as the NHHRC’s recommendation to link funding with a health care home (i.e., a single primary health care service that people with chronic disease would voluntarily register with to ‘help to coordinate, guide and navigate access to the right range of multidisciplinary health service providers’); [16] (2) offering financial incentives to improve the quality of health care services; [17] (3) facilitating improved communication and information-sharing across multidisciplinary health services through the use of electronic health records; (4) changing the way the primary health care team work together (e.g., by introducing a care facilitator and making case conferences easier to organise); [18] and (5) allowing practices to more easily review their performance and make any necessary adjustments.

Intervention 1 of the DCP tests improvements that could be made within the current funding model and focuses on information, communication and education. Intervention 2 includes the same components as Intervention 1, as well as altered funding to support voluntary patient registration with practices (‘health care homes’), incentive payments and funding for a care facilitator. The objective of the trial is to compare the impact of these two interventions on clinical quality and patient and provider experience, and to determine if the interventions allow care to be provided in more flexible ways. The DCP also seeks to determine if these interventions are economically sustainable and scalable nationally. The findings from this project will be used to make recommendations for health policy changes in Australia.

## Methods/Design

### Study design

The Diabetes Care Project is a pragmatic, cluster randomised controlled trial with three parallel arms. Clustering is at the level of the general practice. A cluster design is used to minimise contamination between intervention and control participants.

### Research objectives

The project is designed to: (1) evaluate the impact of the two interventions (in comparison with usual care) on clinical outcomes in adults with diabetes mellitus, patient quality of life, continuity of care, multidisciplinary collaboration and interaction, and patient and provider satisfaction and empowerment; (2) determine if the interventions allow care to be provided in more flexible ways; and (3) determine whether the interventions are scalable nationally and economically sustainable.

### Recruitment

Seven Medicare Locals/Divisions of General Practice (independent entities that are responsible for coordinating local primary health care services) [19] across the states of Queensland (n = 4), South Australia (n = 2), and Victoria (n = 1), Australia, are taking part in the trial. Prior to the commencement of the trial, each Medicare Local/Division of General Practice distributes study information sheets to all general practices (clusters) within their network and seeks expressions of interest to participate in the trial. Practices that express an interest in participating in the trial are enrolled in the project and randomly assigned to one of three treatment groups: control group, Intervention 1 or Intervention 2 (Figure 1). It is expected that fifty general practices will be enrolled in each group. Each enrolled practice is required to undergo training to familiarise themselves with the assigned intervention and study procedures. Medicare Locals/Divisions of General Practice that are assigned to Intervention 2 are supported by a ‘trial delivery and integration team’ to recruit and train care facilitators.

**Figure 1 F1:**
[figure not shown]
Flow chart of Diabetes Care Project.

All eligible patients with diabetes are identified by the enrolled practice and the trial delivery and integration team and sent a GP-endorsed letter advertising the trial and actively seeking enrolments. A participant information sheet and all relevant consent forms are enclosed with this letter. A follow-up telephone call is made to all patients (either by the care facilitator, practice nurse or Medicare Local/Division of General Practice support person) to encourage participation and answer questions. After receiving informed consent, participants are asked to complete the baseline surveys and to meet with their GP to have their baseline metrics recorded. Participant recruitment commenced in April 2012, and patient participation will be completed by February 2014. The planned end date for the trial is June 2014.

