Practices assigned to Intervention 2 experience four changes: access to cdmNet; altered funding arrangements; the provision of a care facilitator; and access to training and capability building. Coordinated care is facilitated through the use of the cdmNet decision support service (as in Intervention 1), but with the addition of risk stratification. Patients are stratified into one of four risk categories based on whether they have complications associated with diabetes (e.g., peripheral neuropathy, background diabetic retinopathy, foot ulceration) and whether their diabetes is under control (uncontrolled diabetes requiring additional allied health services is defined as either HbA1c >7.5% [>58.5 mmol/mol], systolic blood pressure >150 mmHg, total serum cholesterol >5.0 mmol/l, or systolic blood pressure >140 mmHg plus total serum cholesterol >4.5 mmol/l). The four risk categories are characterised as follows: (1) not complex and within range; (2) complex and within range; (3) not complex and out of range; and (4) complex and out of range (see Figure 2). The care plan that is generated for the patient reflects the minimum care needs of individuals in their respective strata, as informed by best practice guidelines. Care in Intervention 2 is also coordinated through the provision of a full-time care facilitator (a tertiary-qualified health professional with experience in primary health care delivery), whose role is to assist the multidisciplinary team in delivering care in accordance with the agreed care plan. The care facilitator has a case load of approximately 300 to 400 patients across all four risk strata.

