**Figure 2 F2:**
[figure not shown]
**Overview of risk stratification categories**^**#**^**.** HbA1c = Glycosylated haemoglobin; SBP = Systolic blood pressure. ^#^These risk stratification categories apply to participants with type 2 diabetes. Participants diagnosed with type 1 diabetes will be provided with the same level of resources as persons in the ‘out-of-range/complex’ category. Newly diagnosed patients will receive the support designated from their category plus additional support for introductory needs.

The altered funding arrangements that are tested in Intervention 2 comprise three components: flexible funding for general practices; pay-for-performance payments for general practices; and flexible funding for allied health professionals. Flexible funding for general practices provides upfront, lump sum funding for all patients who are voluntarily enrolled in the trial at a given practice, which is adjusted according to the risk of the patient population. This funding is used to fund care planning activities for those patients who require it (and is paid once a patient is enrolled rather than for completion of any specific activities) but it does not replace usual GP consultation fees covered by Medicare (Australia’s universal healthcare system). Pay-for-performance payments reward practices for improvements in patient clinical outcomes, meeting pre-defined levels of positive patient experience and completing pre-defined clinical processes. Flexible funding for allied health professionals is accessed on a fee-for-service basis, drawing on a risk-adjusted allowance for each patient. Participants in the control group, Intervention 1 and Intervention 2 will receive their respective care for a period of approximately 18 to 22 months (depending on when they are risk stratified).

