Two potential drawbacks of the trial design are that Medicare Locals/Divisions of General Practice only support one of the two interventions, and that patients are enrolled after practices have been randomised. It was necessary to retain both of these design features in order to make the trial workable. Firstly, requiring practices to support both interventions would have placed impossible demands on general practitioners, allied health professionals and Medicare Locals/Divisions of General Practice. The DCP’s approach means that Medicare Locals/Divisions of General Practice need only train practices in, and provide support for, one of the interventions, and any bias between Medicare Locals/Divisions of General Practice will be detected and corrected for by the DCP’s evaluation team. Secondly, postponing randomisation until patient enrolment was complete would have added a delay of six months (following initial sign up) for patients starting in the trial, and would have required control practices to be trained in the intervention in order for patients to give informed consent, thus confounding results.

The overall design of the trial is driven by the need to find practical and workable solutions to improving diabetes management in Australia that are informed by front-line experience. The trial has been developed through consultation with clinicians and patients during the design phase, and the project receives regular input from the national Diabetes Advisory Group, which comprises seventeen leaders of professional bodies representing various clinicians and people with diabetes. The consortium that is delivering the project consists of over twenty organisations (including Medicare Locals/Divisions of General Practice, state-based primary care organisations, state health departments and universities), and the project runs quarterly feedback forums with participating clinicians and patients.

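### Patients are identified, telephoned and consented after the practice knows its arm, with a caller role and an enrolment payment that belong to Intervention 2 only, and no stated safeguard against differential consent

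*Protocol article*

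**What the plan says.** All references are to the protocol article.

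- **Order of events.** The Discussion states that "patients are enrolled after practices have been randomised" and lists this as a potential drawback. Under Recruitment, "Each enrolled practice is required to undergo training to familiarise themselves with the assigned intervention and study procedures", so the practice knows its arm.
- **Identification.** "All eligible patients with diabetes are identified by the enrolled practice and the trial delivery and integration team" (Recruitment). They are then sent a letter endorsed by the GP.
- **Calls.** "A follow-up telephone call is made to all patients (either by the care facilitator, practice nurse or Medicare Local/Division of General Practice support person"), and the purpose is "to encourage participation and answer questions" (Recruitment). Baseline metrics are recorded after consent.
- **Arm-specific role.** Under Interventions: "Practices assigned to Intervention 2 experience four changes: access to cdmNet; altered funding arrangements; the provision of a care facilitator", together with training. Intervention 1 has two changes, cdmNet and training, and control is usual care.
- **Arm-specific payment.** Flexible funding in Intervention 2 provides "upfront, lump sum funding for all patients who are voluntarily enrolled in the trial at a given practice" (Interventions). It is risk-adjusted and falls due on enrolment. Intervention 2 practices are also paid for improvement in clinical outcomes.
- **Analysis.** The primary endpoint is the between-group difference in change in HbA1c. It is tested by the time/group interaction in a mixed model adjusted for clustering and the stratification factors (Statistical analysis).

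**The concern.** Randomising practices balances practices. It does not balance the patients who agree to join once the arm is known. Here the people who list and telephone patients can know the arm. One of the three named caller roles is part of one intervention, and only that intervention's practices are paid on enrolment. If patients in Intervention 2 are persuaded more often, or are a different kind of patient, the arms can differ at baseline for reasons unrelated to treatment. Where that difference lies in temporarily raised HbA1c, later values fall back towards the mean without any effect of care, and a comparison of change counts the fall as benefit.

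**Working it through.** **1. What the stated procedures establish.** Three facts stand in the text: allocation precedes enrolment, the practice is trained in its arm, and the call is meant to persuade as well as inform. The facilitator role and the enrolment payment belong to Intervention 2.

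**2. Whether a stated safeguard covers differential consent.**
- The researcher blinded to practice identity (Randomisation) protects the allocation of practices only.
- The Discussion promises to detect and correct bias between Medicare Locals/Divisions. Control and intervention practices are randomised 1:2 inside the same Medicare Local/Division, so differential consent between arms arises within these units and is not what that promise addresses.
- Stratified blocks and intention-to-treat act on practices and on patients already enrolled. Neither acts on who consents.

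**3. Whether the stated reasons require the present procedure.** The Discussion gives two: a six-month delay if randomisation waited for enrolment to finish, and control practices needing intervention training so that their patients could give informed consent. Both concern completing enrolment and consent before randomisation. Neither concerns when the list of eligible patients is extracted, or which role telephones.

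**4. Illustrative size.** The plan gives no figure for this bias, so there is none to reproduce. Inputs:
- Target difference 0.25 points (Primary outcome; Sample size calculation).
- Baseline imbalance d of 0.1, 0.2 or 0.3 points: assumption.
- Correlation r between baseline and follow-up HbA1c of 0.5 to 0.8: assumption. The Sample size calculation attaches that description to its value of 0.05. But 0.05 is used there as an intracluster correlation: 1 + (50 − 1) × 0.05 = 3.45, the stated design effect. It is therefore not used as r here.

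If selection acts on the measured baseline value, both arms share a common mean, and variances are equal at both times, the spurious difference in change is (1 − r) × d:

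| d | r = 0.8 | r = 0.5 | share of 0.25 |
|---|---|---|---|
| 0.1 | 0.2 × 0.1 = 0.02 | 0.5 × 0.1 = 0.05 | 8% to 20% |
| 0.2 | 0.2 × 0.2 = 0.04 | 0.5 × 0.2 = 0.10 | 16% to 40% |
| 0.3 | 0.2 × 0.3 = 0.06 | 0.5 × 0.3 = 0.15 | 24% to 60% |

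**5. The opposite case.** If the imbalance reflects stable differences, such as longer or more complicated disease, it persists at follow-up. The difference in change is then d − d = 0. A baseline-adjusted comparison, with within-arm slope about r, would instead show d − r × d = (1 − r) × d against the arm with the higher baseline. That is the same size as in the table, with the sign reversed. Neither analysis is safe under both mechanisms, so both are needed.

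**6. Timing.** Baseline is recorded after consent. If selection acted on earlier values in the practice record, part of the fall would occur before baseline, and the table would overstate the remainder.

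**The case against.** The strongest case on the other side is that the drawback is disclosed and defended, and that a condensed article may leave calling procedures and covariates to fuller documents. All eligible patients are to be written to and telephoned, the delivery team shares in identifying them, and the entry criteria are mostly objective. Baseline characteristics by group and reporting to the CONSORT cluster extension are already promised, so a baseline imbalance would show.

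Much of this stands. Universal invitation largely closes selection at the invitation step and leaves persuasion and consent. The disclosure settles that enrolment follows randomisation, but it does not deal with who lists and who calls, and the article does state those procedures.

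Three stronger readings are tempting but not supported:

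- **That callers do differ by arm.** The article names three alternative callers without splitting them by arm. Facilitators are recruited through Medicare Locals/Divisions that also contain control practices, and the text does not say whether they telephone control patients.
- **That the payment rewards enrolling higher-risk patients.** A risk adjustment may only offset the extra care-planning work.
- **That the change comparison will be biased in favour of Intervention 2.** That needs selection on transient HbA1c. With stable differences it does not follow, and the document fixes neither mechanism nor direction.

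Nothing in the article suggests that the invitation letters differ between arms, so the letters are no part of this point.

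**Conclusion.** The point holds as a risk built into stated procedures that could be reduced cheaply. It is not a demonstrated bias. Listing, calling and consent follow disclosure of the arm, one permitted caller role and the enrolment payment are specific to Intervention 2, and no safeguard against differential consent is stated. The direction and size cannot be derived from the document. The range of 0.02 to 0.15 points (8 to 60% of the 0.25-point target) is conditional on an assumed imbalance of 0.1 to 0.3, an assumed correlation of 0.8 to 0.5, and selection on transiently high HbA1c. Under stable differences the bias in the change comparison is little or none.

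**What to change.** 1. Have each practice extract and lodge its list of eligible patients before its allocation is disclosed. Randomisation already waits for three practices in a stratum, and practice software must already be compatible with project software for data extraction. The cost is a short delay before disclosure.
2. Have recruitment calls made by the same role in all arms, for example the Medicare Local/Division support person already named, and not by the care facilitator. This equalises callers but does not blind them, since the Medicare Locals/Divisions also support the intervention. What patients are told for consent may still have to differ by arm. The cost is some shift of calling workload.
3. Adjust the primary comparison for baseline HbA1c, which is already collected, and keep the unadjusted change comparison as a sensitivity analysis. Adjustment does not remove selection on unmeasured or stable traits. If the two results diverge, report both and discuss the likely mechanism.
4. Report enrolled/eligible numbers and baseline HbA1c by arm.

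Recruitment began in April 2012 and participation ends by February 2014. With at least 18 months of care, enrolment would close around August 2012. Once recruitment is complete, only items 3 and 4 apply.
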